### Statistical plan

Summary statistics and visualizations will be produced to describe the variables of interest. Study participants (N=200) will be characterized in terms of demographics and clinical variables using percentages for categorical variables and either means and standard deviations or median and interquartile range for continuous variables. We will assess differences in characteristic distributions by group using independent *t* tests or corresponding nonparametric tests (Wilcoxon Rank Sum) and Chi-squared tests (or Fisher’s Exact test for small sample sizes), as appropriate. Two-tailed tests will be performed using the R Stats Package (version 4.4.1). *P* values will be reported with three decimal digits, and *P* < 0.05 will be considered significant. We will evaluate the study hypotheses using univariable and multivariable linear mixed-effects models (LMM) and logistic regression. LMMs will be used for continuous outcomes (hypotheses 1, 2, and 3 for continuous blood pressure). Logistic regression models will be used for binary outcomes (hypothesis 3 for nocturnal dipping, hypothesis 4). In the case of ordinal outcomes, proportional odds cumulative logit (POCL) will be the statistical test of choice (hypothesis 5). Each outcome will be analyzed individually.

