### Recruitment

Service members who were injured in combat will be eligible for this study if they are (1) at least 18 years old, enrolled in WWRP, and previously agreed to be contacted about future research opportunities, and (2) able to complete the informed consent process, receive mailed study devices, and complete laboratory procedures within the US. Subjects that are unable to complete the informed consent process, be mailed study devices, or complete laboratory draws within the US will be excluded. Two groups of combat-injured participants (n = 100 per group) will be recruited. This study has been powered to detect an unadjusted period prevalence difference of 0.15 between the severely injured (ISS ≥ 14; assumed 25% prevalence) and minimally injured (ISS ≤ 3; assumed 10% prevalence) groups, with n = 100 per group, two-sided α = 0.05, and 80% power. The first group will comprise severely injured participants with an ISS ≥ 14. If enrollment targets are not met with this cutoff score, the study team will consider enrolling participants with an ISS ≥ 11 in the severely injured group. The second group will include minimally injured participants, defined as ISS ≤ 3. Cutoff scores were determined by assessing the ISS distribution among eligible WWRP participants, and then estimating the number of SPIRIT study candidates needed in each group to enroll 100 participants per group. Based on previous recruitment rates in the aforementioned pilot study [11], we estimated the expected enrollment rate for the SPIRIT study to be roughly 30%. NHRC staff have shared contact information for potentially eligible WWRP participants with the USUHS Military Cardiovascular Outcomes Research (MiCOR) Program team. Research staff at MiCOR will contact study candidates via phone to assess their willingness to participate, verify eligibility, and schedule a remote study visit to complete the informed consent process. Participants will review and sign the informed consent and Health Insurance Portability and Accountability Act of 1996 (HIPAA) authorization forms using a digital signature tool in REDCap (Research Electronic Data Capture) hosted at USUHS [18,19].

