Participants will be mailed three wearable devices with instructions for use: (1) an ambulatory electrocardiogram (ECG) monitor to be worn for seven consecutive days; (2) a Home Sleep Test (HST) device to be worn on the second or third study day, and (3) a 24-hour ambulatory blood pressure monitor (ABPM) to be worn on the day following the HST. Participants will subsequently mail all wearable devices back to the respective service providers or the USUHS study team, as appropriate, who will complete the device data extraction. The ambulatory ECG monitor will record one-lead ECGs to evaluate SNS activation. In addition to heart rate and heart rate variability (HRV) measures, QT intervals and their variability (QTV) will be measured. The ambulatory ECG will also determine the incidence and nature of arrhythmias, including premature ventricular contractions (PVC), the incidence of atrial fibrillation, as well as atrial and ventricular tachycardia. The frequency of episodes of atrial fibrillation or atrial flutter lasting longer than five minutes, the PVC density (percentage of total heartbeats that are PVCs), and the frequency of ventricular tachycardia will be captured from these reports. Heart rate, HRV, and QTV measures will be automatically calculated for each five-minute epoch of the ECG recordings. HRV time-domain measures include the standard deviation of beat-to-beat intervals (SDNN) and root mean square of successive differences (RMSSD). HRV frequency domain measures include low-frequency (LF, 0.04–0.15 Hz) and high-frequency (HF, 0.15–0.4 Hz) power components and the LF/HF ratio. QTV measures include log-transformed QT variance (logQTv) and beat-to-beat QT variability index (QTVI).

The presence of comorbid OSA and nocturnal hypoxemia will be evaluated with the HST. The HST device will be worn during sleep on the second study day. Blood pressure will be measured using the 24-hour ABPM, the gold standard for assessing HTN [28]. Mean 24-hour blood pressure and mean blood pressure during sleep have the most robust association with long-term major cardiovascular events among all blood pressure-related measures [29]. The ABPM will be worn during the 24 hours following the HST. The mean blood pressure for the entire 24 hours of wear and the sleep time will be computed. Nocturnal dipping and the drop in blood pressure during sleep will also be assessed.

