### Objectives and hypotheses

The primary objectives of this study are two-fold: firstly, we will collect robust ambulatory ECG and blood pressure data at a single time point from cohorts of severely injured (ISS ≥ 14, n = 100) and minimally injured (ISS ≤ 3, n = 100) current and former service members; secondly, we will examine the associations between ECG variables, sleep characteristics, mental health, SNS activity, and physical health outcomes including HTN. We will test the following five hypotheses:

*Hypothesis 1:* Severely injured service members have higher cardiovascular risk as defined by the pooled cohort equation (a tool for estimating the 10-year risk of CVD, it includes age, race, total cholesterol, HDL cholesterol, systolic blood pressure, blood pressure medications, diabetes, smoking [30]) and hsCRP (a validated serologic marker of CVD risk [31,32]) compared to minimally injured service members.

*Hypothesis 2:* Severely injured service members have higher levels of SNS activity and arrhythmia burden (as evaluated by ECG monitor) compared to minimally injured service members.

*Hypothesis 3:* Severely injured service members have higher 24-hour mean blood pressure and less nocturnal dipping (as evaluated by ABPM) compared to minimally injured service members.

*Hypothesis 4:* (1) The prevalence of both insomnia symptoms (as defined by ESS and ISI) and OSA (as defined by HST) is greater among severely injured service members compared to minimally injured service members, and (2) the presence of OSA among injured service members correlates strongly with HTN and other cardiovascular comorbidities.

*Hypothesis 5:* Mental health symptoms (PTSD symptoms, depressive symptoms, and dissociative experiences, as defined by the PCL-5, PHQ-8, and DES-B) will be significantly associated with SNS hyperactivity, sleep disorders, and cardiovascular risk, and this association will differ by injury severity.

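### The only analysis named for the dipping part of hypothesis 3 is a binary one, although the continuous sleep-time fall in blood pressure is already measured and would give more power

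*Protocol article*

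**What the plan says.** Hypothesis 3 (Objectives and hypotheses) has two parts. The severely injured are expected to have a higher 24-hour mean blood pressure and "less nocturnal dipping (as evaluated by ABPM) compared to minimally injured service members".

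Under Data collection, mean pressure is to be computed for the whole 24 hours and for sleep. The section adds: "Nocturnal dipping and the drop in blood pressure during sleep will also be assessed".

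The Statistical plan divides hypothesis 3 by type of outcome. Linear mixed-effects models are for continuous outcomes, including continuous blood pressure under hypothesis 3. For dipping it says: "Logistic regression models will be used for binary outcomes (hypothesis 3 for nocturnal dipping, hypothesis 4").

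The sample size (Recruitment) is not specific to dipping: "Two groups of combat-injured participants (n = 100 per group) will be recruited", and "This study has been powered to detect an unadjusted period prevalence difference of 0.15" between an assumed 25% in the severely injured and 10% in the minimally injured, "with n = 100 per group, two-sided α = 0.05, and 80% power". The outcome with those rates is not named.

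**The concern.** A hypothesis of less dipping is most directly tested by comparing the size of the fall between groups. A binary version treats someone just below the threshold as wholly different from someone just above it, and treats all participants on one side as alike. The comparison then has less power for the same participants, and its result depends on where the threshold sits.

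What is at stake is a false null on a named hypothesis. The Limitations section already concedes that 100 per group limits power. A non-significant dipper comparison could be read as evidence against a link between injury severity and dipping, when the fall itself might have shown one.

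This is a choice that the article states, not a detail left to a fuller document. The lack of a stated cut-off is not the criticism; an article may well leave that to the full protocol or analysis plan.

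**Working it through.** **Inputs from the article:** n = 100 per group; two-sided α = 0.05; 80% power; 10% v 25% for an unnamed outcome (all from Recruitment).

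**Assumed, because the article gives nothing for dipping:** the percentage fall is normal with the same SD in both groups; one cut-off defines non-dippers; ABPM data are complete; the comparison is unadjusted. Write d for the group difference in SD units, p0 for the non-dipper proportion in the minimally injured and p1 for that in the severely injured.

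**Formulas**
- Binary: power = Φ{[(p1 − p0) − 1.96·√(2p̄(1 − p̄)/n)] / √([p0(1 − p0) + p1(1 − p1)]/n)}, where p̄ is the mean of p0 and p1.
- Continuous: power = Φ(d·√(n/2) − 1.96).
- Link between the two: p1 = Φ(z(p0) + d).

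**Step 1. Reproduce the stated design.** With 0.10 v 0.25, p̄ = 0.175. The null SE is √(2 × 0.175 × 0.825/100) = 0.0537 and the alternative SE is √((0.09 + 0.1875)/100) = 0.0527. Power = Φ((0.15 − 1.96 × 0.0537)/0.0527) = 80.2%, and the required n is 100 per group. The article's figure reproduces.

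**Step 2. Same rates, taken as if they were non-dipper rates.** The implied difference is d = z(0.90) − z(0.75) = 1.282 − 0.674 = 0.607. Continuous power = Φ(0.607 × 7.071 − 1.96) = 99.0%, against 80.2% binary. The loss is about 19 points.

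**Step 3. Assumed difference d = 0.4, assumed cut-off 10%, assumed SD 6 points.** Continuous power is about 80% (two-sample t test).

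| Assumed mean fall, minimally injured | Non-dippers, minimal v severe | Binary power | n per group for 80% binary |
|---|---|---|---|
| 12% | 36.9% v 52.7% | 61% | 156 |
| 13% | 30.9% v 46.0% | 60% | 160 |
| 15% | 20.2% v 33.2% | 55% | 181 |

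For the first row, p0 = Φ((10 − 12)/6) = Φ(−0.333) = 0.369 and p1 = Φ(−0.333 + 0.4) = 0.527. The losses are 80 − 61 = 19 to 80 − 55 = 25 points.

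**Step 4. Vary the non-dipper prevalence.** Set d = (1.96 + 0.842) × √(2/100) = 0.396, so that the continuous test has exactly 80% power.

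| p0 | 10% | 20% | 30% | 40% | 50% | 60% | 70% |
|---|---|---|---|---|---|---|---|
| Binary power | 42.5% | 53.8% | 58.7% | 60.4% | 59.8% | 57.1% | 52.1% |
| Loss (points) | 37.5 | 26.2 | 21.3 | 19.6 | 20.2 | 22.9 | 27.9 |

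**Step 5. Vary both.** Over d = 0.2 to 0.6 and p0 = 10% to 70%, the smallest loss is 6.8 points (d = 0.6, p0 = 40%: 98.9% v 92.1%). The largest is 37.5 points (d = 0.4, p0 = 10%: 80.7% v 43.2%). The binary test loses in every cell.

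**The case against.** **The continuous fall may be analysed as well.** Data collection lists the sleep-time drop beside dipping as a quantity to be assessed, and the linear model for continuous blood pressure could be read to cover it. A reader might infer that dipping will be tested only as a binary outcome; the article does not establish that. This stands. What remains is that no model is named for the drop, while dipping is placed by name under logistic regression. The text does not say that the continuous drop tests hypothesis 3.

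**The binary analysis fits the design.** The study is powered on a difference in proportions, and at 10% v 25% a binary outcome has the stated 80%. This also stands: power of 55 to 61% follows from an assumed effect of 0.4 SD, not from any figure in the article. But at the article's own rates the continuous analysis would still do better, at 99%.

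**Dipper status has meaning of its own.** The Introduction speaks of losing a healthy dipping pattern, and less dipping can mean fewer dippers. That is a good reason to report the category. It does not make the category the stronger test of the hypothesis, and reporting it as a secondary result keeps its interpretive value.

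**Conclusion.** The point holds in a limited form. For the dipping part of hypothesis 3, the one named analysis is logistic regression on a binary outcome, although the hypothesis concerns degree and the continuous drop is already to be assessed.

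The direction of the loss is firm under the normal, equal-SD model. Its size is not. About 20 points is typical when the continuous test has about 80% power and the cut-off lies near the middle of the distribution, and also at the article's 10% v 25% if those rates are applied to dipping. The range over the scenarios tried is about 7 to 38 points. A reader might take 20 points as a property of this study; the article gives no dipping inputs that would support one fixed figure.

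Nor does it follow that hypothesis 3 as a whole is underpowered. Its 24-hour mean blood pressure part is analysed as continuous and loses nothing. This is a change the plan should make, not a flaw that invalidates it.

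**What to change.** In the Statistical plan, name the continuous sleep-time drop in blood pressure as the main dipping analysis for hypothesis 3, compared between ISS groups with the plan's linear model for continuous outcomes. Keep dipper v non-dipper by logistic regression as a secondary summary. This would also settle which of the two quantities listed under Data collection tests the hypothesis.

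The cost is a phrase or two of text. It needs no new data, devices or participants, and the sample size does not change.

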## Discussion

In this cross-sectional study of minimally and severely injured combat casualties living throughout the US, we will collect ambulatory, at-home (ECG, HST, and 24-hour ABPM), laboratory, and survey-based data on cardiovascular function, sleep behavior, mental health, SNS activation, and physical health outcomes. The primary objectives of this study will be to (1) collect robust ambulatory ECG and blood pressure data from the target study population and (2) use these data to examine combat injury severity in relation to the identified mental, behavioral, and physical health outcomes.

Given that many of the more than 53,000 post-9/11 combat casualties are still living with the long-term effects of their injuries, and that future large-scale combat operations could result in many more casualties [33], it is critical to better define and identify targets for intervention to reduce long-term health risks among combat-injured military personnel and veterans.

While CVD, HTN, sleep disorders, and mental health concerns are more common in injured service members compared to non-injured service members, it is important to note that these various outcomes do not occur in isolation and that the relationships may be bidirectional. For example, insomnia is associated with subsequent PTSD, depression, and anxiety [8], and mental health conditions increase the risk for subsequent insomnia [7]. Furthermore, PTSD has been associated with both activation of the SNS [34] and inflammation [35] in veterans, while markers of SNS activation are associated with both insomnia [36] and inflammatory markers [37]. Sleep disorders, which are common in military and veteran populations [38,39], are associated with an increased risk of HTN [40], cardiac arrhythmias [41], and sudden cardiac death [42,43]. Poor quality sleep and diagnosed sleep disorders may, therefore, represent a common pathway for both cardiometabolic disease and mental health outcomes among survivors of combat-related injury, as well as a potential target for therapeutic interventions. Given this body of evidence, the mechanisms that link sleep disorders and mental health conditions to CVD and HTN are likely to be complex and interrelated, as shown in our conceptual model (Fig 1). Data collected during the SPIRIT study will be used to test multiple hypotheses related to this conceptual model.

**Fig 1 pone.0321035.g001:**
[figure not shown]
The conceptual framework for the pathways between combat injury and subsequent adverse physical health outcomes. SNS, Sympathetic nervous system; HR, Heart rate; SVR, Systemic vascular resistance; OSA, Obstructive sleep apnea; PTSD, Posttraumatic stress disorder; hs-CRP, High-sensitivity C-reactive protein; HTN, Hypertension; CVD, Cardiovascular disease.

### Related ongoing studies

The Long-term Impact of Military-Relevant Brain Injury Consortium - Chronic Effects of Neurotrauma Consortium (LIMBIC-CENC) Prospective Longitudinal Study (PLS) is perhaps the largest ongoing, prospective investigation of injured US service members, with over 1,700 combat veterans enrolled as of 2021, and a goal of 3,000 participants by 2024 [44]. However, the primary exposure of interest in the LIMBIC-CENC PLS is mild TBI sustained in combat, with more than 80% of participants having a history of at least one mild TBI. Other large, longitudinal studies of US veterans of recent conflicts have either focused on a single service branch and primarily examined mental and behavioral health outcomes [45], or in the case of the WWRP, examined the effects of combat injury using only patient-reported outcomes and retrospective record review (i.e., no objective, laboratory, blood-based or wearable device data) [13].

Outside the US, the Armed Services Trauma and Rehabilitation Outcome (ADVANCE) research initiative is a large-scale longitudinal study of mental and physical health outcomes in male combat-injured service members from the United Kingdom (UK). Using a variety of in-person tests and survey assessments, investigators from ADVANCE are examining the long-term impact of combat injury on outcomes such as musculoskeletal disease, cardiovascular risk and disease, and mental health outcomes in 600 UK service members injured in Afghanistan matched to 600 combat-deployed, non-injured service members [46]. Since the start of enrollment in 2016, findings from the ADVANCE study have already shown associations between combat injury and subsequent long-term health outcomes, including mental health and cardiovascular outcomes [47–52].

Like SPIRIT, ADVANCE collects laboratory data to include blood counts, chemistries, hemoglobin A1C, hsCRP, and lipids, evaluates blood pressure and HRV, and uses validated survey measures to assess sleep. Although ADVANCE and SPIRIT both utilize physical health and self-report measures, SPIRIT will supplement ADVANCE in several ways. Most importantly, ambulatory/at-home devices will be used to collect additional data in SPIRIT, including an ambulatory ECG monitor worn for seven consecutive days (compared to two consecutive five-minute recordings in ADVANCE), a 24-hour ABPM, which is the gold standard for the diagnosis of HTN (compared to central and peripheral blood pressure measurements in ADVANCE), and an HST device (compared to no sleep test in ADVANCE). Using these wearable devices will allow us to obtain, with high granularity, robust measurements of cardiovascular function and sleep disturbances. Moreover, wearable devices (compared to in-person tests in ADVANCE) will enable us to recruit broadly from the overall population of combat-injured service members throughout the US. Without remote recruitment and participation, the SPIRIT study would be limited to either studying only participants living in a particular geographic region or enrolling only participants willing and able to travel to a study site. Lastly, currently, the ADVANCE study only enrolls male UK service members. SPIRIT, however, will enroll both male and female combat-injured service members.

### Limitations

There are several limitations to the SPIRIT study. First, the cross-sectional design will only examine one point in time. Future longitudinal studies are required to better define the risk of adverse long-term outcomes in combat casualties and the prospective nature of associations among different risk factors. Second, the overall number of participants is modest (n = 100 per group), which will limit statistical power, particularly for analyses involving less-common outcomes or low prevalence injuries (e.g., TBI). Third, since the study is observational, the findings will be correlative and cannot be used to infer causation. Lastly, there may be selection bias as subjects who respond to the invitation may differ from those who decline the invitation to participate in the study. On completion of recruitment, subjects who opted to be enrolled in the study will be compared to those who did not to assess for potential selection bias.

### Future research

The long-term goal of this research effort is to identify the most promising targets for future interventional investigations, such as randomized controlled trials (RCT), to improve outcomes in survivors of combat injury. These targets could include aggressive treatment of sleep-disordered breathing and hypoxemia by instituting early continuous positive airway pressure (CPAP), more aggressive treatment of HTN, more aggressive treatment of PTSD, or a combination of these treatments. Further RCTs would be needed to test any of these interventions. The data acquired in this study will be critical to planning a successful RCT intended to improve the clinical management of combat veterans.

## Conclusions

Retrospective examinations of administrative and medical data indicate that combat-injured service members are at higher risk for the development of adverse long-term health outcomes relative to non-injured combat-exposed service members. However, existing research in this area has been limited. The SPIRIT study represents an important step towards a more comprehensive understanding of the long-term impact of combat injury on physical, mental, and behavioral health. The results will be a foundation for subsequent studies of targeted prevention and interventions in this vulnerable population.
